### **6.1.2. Site Selection Criteria**

Rheumatology, dermatology and non-Rrheum/non-derm sites will be selected based on their patient population targeted for this study and their ability to appropriately conduct the study. The non-rheum/non-derm sites may include primary care practices, orthopedists, ophthalmologists, physiatrists and podiatrists according to the standard practice in the respective country.

The sample of sites will be recruited to be broadly representative of the settings providing medical care for PsA patients in the respective country.

### **6.1.3. Number of patients**

Approximately 1.200 patients will be included in the study. The study will cover sites in around 15 countries in Western and Eastern Europe, Latin America and Asia.

## **6.2. Study Duration**

This is a cross-sectional, observational study. The inclusion period will be approximately 16-18months.

## **6.3. Description of Activities**

For the management of PsA patients a regular collaboration between different specialties is advised by established clinical recommendations (28-31, 34, 35). Consulting visits for current PsA disease assessments by dermatologist and/or rheumatologists, depending on the recruiting site, usually happens between a 12 weeks period after a routine visit at the recruiting site.

The following will be documented:

### Recruiting site – Module 1

- Socio-demographic information
- PsA symptoms and diagnosis
- Relevant medical history
- Relevant co-morbidities
- PsA treatment
- Administration of patient questionnaires

If the recruiting site is a rheumatologist, the rheumatology module 2 will be used in addition.

If the recruiting site is a dermatologist, the dermatology module 3 will be used in addition.

### Rheumatology Module 2

- TJC/SJC (66/68)
- Enthesitis count
- Dactylitis count
- PtGA
- CRP/ESR (if available)
- Imaging data (if available)
- Components of ASDAS (for patients with back pain only)

### Dermatology Module 3

- BSA
- PGA
- Psoriatic nails (count)
- Musculoskeletal signs

This study will assess PsA disease burden by using validated Patient Reported Outcome (PRO) instruments. Validated translations of these patient questionnaires will be administered as paper format.

The following questionnaires will be used:

- **SF12v2:** This Quality of Life survey asks for the patient's view about his/her health, how the patient feels and how well he/she is able to do the usual activities. The questionnaire consists of 12 questions, should require approximate 8 minutes to complete and is presented in Appendix A.
- **HAQ-DI** (Health Assessment Questionnaire Disability Index): It consists of 15 questions assessing the patients' physical function and health-related quality of life. The questionnaire should require approximate 12 minutes to complete and is presented in Appendix B.
- **WPAI PsA** (Work Productivity and Activity Impairment Questionnaire): It consists of 6 questions assessing the impact of the disease on the ability of the patient to work and perform normal daily activities. The questionnaire should require approximate 7 minutes to complete and is presented in Appendix C.
- **DLQI** (Dermatology Life Quality Index): the aim of this questionnaire is to measure how much the skin problem has affected the life of the patient. The questionnaire consists of 10 questions which should require approximate 5 minutes to complete and is presented in Appendix D.

Confidential Information

No use or disclosure outside AbbVie is permitted without prior written authorization from AbbVie

**Table 1. Schedule of Assessments**

| Assessments                                            | General Data    | Musculoskeletal Signs | Skin Signs    |
|--------------------------------------------------------|-----------------|-----------------------|---------------|
|                                                        | Recruiting site | Rheumatologist        | Dermatologist |
| Patient authorization/Informed consent                 | X               |                       |               |
| Socio-demographic data                                 | X               |                       |               |
| PsA symptoms                                           | X               |                       |               |
| Relevant medical history                               | X               |                       |               |
| Relevant co-morbidities                                | X               |                       |               |
| PsA treatment                                          | X               |                       |               |
| Confirmation of PsA (per country Health Care System)   | X               | X                     | X             |
| TJC/SJC (66/68)                                        |                 | X                     |               |
| Enthesitis count                                       |                 | X                     |               |
| Dactylitis count                                       |                 | X                     |               |
| PtGA                                                   |                 | X                     |               |
| CRP /ESR (if available)                                |                 | X                     |               |
| Imaging data (if available)                            |                 | X                     |               |
| Components of ASDAS (for patients with back pain only) |                 | X                     |               |
| BSA                                                    |                 | X                     | X             |
| PGA                                                    |                 |                       | X             |
| Psoriatic nails (count)                                |                 |                       | X             |
| Musculoskeletal signs                                  |                 |                       | X             |
| Confirmation of psoriasis                              |                 |                       | X             |

  

| Patient Questionnaires (PROs) |   |
|-------------------------------|---|
| HAQ-DI                        | X |
| SF-12v2                       | X |
| DLQI                          | X |
| WPAI PsA                      | X |

Confidential Information

No use or disclosure outside AbbVie is permitted without prior written authorization from AbbVie

## 6.4. Event Reporting

This is an observational research study not designed to identify or quantify a safety hazard relating to an AbbVie authorized product.

If a patient reports a product-related event (e.g. suspected adverse reaction or product complaint) to his/her healthcare professional during the data collection period or the healthcare professional identifies a product-related event, which is considered related to any AbbVie authorized product, the event should be reported to AbbVie. Any product-related events considered to be related to a non-AbbVie product should be reported in accordance with local laws and regulations to the relevant Regulatory Authority and/or drug marketing authorisation holder. In the event of a pregnancy occurrence in a patient during the data collection period, the pregnancy should be reported to AbbVie.

Patient Reported Outcome (PRO) or quality of life questionnaires data are not considered a potential source of adverse reactions. However, participating sites should review the PRO or questionnaire(s) data and if a possible product-related event (including a suspected adverse reaction) is noted, the HCP must determine whether the event is related to an AbbVie authorized product and if so, it should be reported to AbbVie

## 7. Ethics and Quality

This observational study will be run in compliance with local laws and regulations. Notification/ submission to the responsible Ethics Committee, Health Institutions and/or Competent Authorities will be done as required by local laws and regulations.

Written patient authorization to use and/or disclose his/her anonymized health data (and informed consent where applicable) will be obtained prior to patient inclusion.

To maintain subject confidentiality, no demographic data that can identify the patient will be collected (e.g. initials, date of birth), only the patient age will be collected. In order to protect patient's identity, a unique number will be assigned to each patient and related study records.

Data Recording Forms (DRF) in English and patient questionnaires in local language will be provided to each site in paper format coded with a unique patient number. The participating site will be asked to send the filled out Forms/Questionnaires regularly to the AbbVie Affiliate office in the respective country (see section 11 Affiliate Agreement page).

### 7.1. Source Documents

The investigator must maintain source documents for each patient in the study, consisting of medical records containing demographic data, medical, treatment and diagnostic documentation.

Confidential Information

No use or disclosure outside AbbVie is permitted without prior written authorization from AbbVie

## 7.2. Quality Assurance

The sites will be instructed in the research plan, the handling of the paper DRFs and the administration of the patient questionnaires.

Continuous oversight of the observational study will be performed by AbbVie or a CRO working on behalf of AbbVie.

## 8. Data Analysis Plan

### 8.1. Endpoints

#### Primary Endpoints

- Time from inflammatory musculoskeletal symptom onset to PsA diagnosis
- Time from PsA diagnosis to first csDMARD
- Time from PsA diagnosis to first bDMARD
- Time from first csDMARD to first bDMARD

#### Secondary Endpoints

- PsA disease activity
  - Joint disease activity (TJC/SJC, enthesitis count and dactylitis count, axial involvement by ASDAS)
  - Skin disease activity (PGA, BSA, psoriatic nails count)
- Disease burden :
  - Physical function (HAQ-DI score)
  - Quality of life (SF12v2.0 score)
  - Work productivity (WPAI scores)
  - DLQI score

### 8.2. Plan for Statistical Analysis

Only patients with a confirmed diagnosis of PsA will be eligible for statistical analysis. The exact definition of the analysis populations will be detailed in a separate statistical analysis plan.

Collected data will be summarized by descriptive statistics. Quantitative variables will be reported as absolute N, mean, standard deviation, median, 1st and 3rd quartiles and minimum and maximum. Qualitative variables will be reported as absolute and relative frequency distributions.

Research outcomes of primary and secondary interest will be analyzed using descriptive statistics overall and in subgroups defined by explanatory variables (disease severity perception by patients and physicians and clinical specialty). Effects will be estimated depending on the scale of the endpoint by use of mean differences or ORs with respective 95% confidence interval. The effect estimates will be calculated from simple regression

Confidential Information

No use or disclosure outside AbbVie is permitted without prior written authorization from AbbVie

models run separately for each of the explanatory variables and thereafter in multiple regression models with variable selection to identify and assess important explanatory variables. Depending on the scale of the dependent variable, linear or logistic models will be used.

PsA clinical manifestation and disease burden will be analyzed using descriptive statistics. Regression analyses will be done as described above, using time from symptom onset to PsA diagnosis, time from PsA diagnosis to first csDMARD, first bDMARD and from first csDMARD to first bDMAD as explanatory variables.

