A number of international and national recommendations for the management of PsA and corresponding treatment algorithms have been published in the past few years in both rheumatology and dermatology (28-31, 34, 35). Ideally, management of PsA should address joints and skin as well as extra-articular manifestations and comorbidities (34, 35). It has been demonstrated that PsA patients receiving a multidisciplinary care, involving both rheumatologists and dermatologists in a US clinic, were more likely to receive systemic medication (25% vs 15%) and be treated with a biologic agent (37% vs 16%) than in prior unidisciplinary care (36).

While consensus is evident among the recommendations on the main treatment principles, the extent to which they are followed by practicing physicians is unknown. In reality it appears that many patients with PsA are not diagnosed, or are undertreated or not treated systematically (34, 37). A recent large population based multinational survey conducted in North America and Europe revealed that approximately 15% of patients with PsA had not seen a health care provider in the past year, and almost 60% were not being treated for their joint disease (38).

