## 4. Rationale

Evidence suggests that timely and effective management can improve long-term outcomes in patients with PsA. The factors influencing management decisions in PsA are not well understood. In the field of diabetes mellitus, the interactions of patient, physician and systemic factors were found to have implications for the implementation of a diabetes management model (39).

Early diagnosis of PsA is the first and crucial step in effective management of PsA, The detection of inflammatory musculoskeletal symptoms drives PsA diagnosis. The clinical patterns of PsA are heterogeneous and may vary in an individual patient over time, which renders recognition of the disease by non-rheumatologists and patients challenging, leading to a delay in diagnosis and worse long term outcomes. Therefore, the time of musculoskeletal symptoms onset is selected in this study as the anchor date for describing different management steps in patients with PsA. In order to assess this aspect in the overall PsA population both patients with established and suspected PsA diagnosis will be asked to participate in the study. Medical care of PsA patients are provided by various clinical specialties, such as rheumatologists, dermatologists, other specialists and primary care practices. In order to describe the overall PsA population, which includes patients with mild disease that are not consulting physicians with rheumatology or dermatology expertise, the study aims to include PsA patients from all specialties providing medical care.

This study is expected to provide important insights into the factors influencing management of PsA, which may aid planning improvements in the standards of care in this chronic systemic disease.

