## 5. Study Objectives

### Primary objective:

- To evaluate the association between the clinical specialty setting and time from inflammatory musculoskeletal symptom onset to PsA diagnose and to different management steps in patients with a confirmed PsA diagnosis

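### The specialty comparison of recorded delays does not adjust for when each interval began, so a difference between settings in time since that start would be read as a specialty effect

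*Protocol*

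**What the plan says.** The primary objective (section 5) is "To evaluate the association between the clinical specialty setting and time from inflammatory musculoskeletal symptom onset to PsA diagnose" and to later management steps. The primary endpoints (section 8.1) start at three different events:

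- symptom onset: "Time from inflammatory musculoskeletal symptom onset to PsA diagnosis";
- diagnosis: time to first csDMARD, and "Time from PsA diagnosis to first bDMARD";
- first csDMARD: "Time from first csDMARD to first bDMARD".

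Section 4 says that "the time of musculoskeletal symptoms onset is selected in this study as the anchor date". Section 6.2 says "This is a cross-sectional, observational study".

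Section 8.2 admits only confirmed patients to the analysis. It summarises outcomes overall and "in subgroups defined by explanatory variables (disease severity perception by patients and physicians and clinical specialty"). It then estimates effects from one simple regression per explanatory variable, followed by multiple regression with variable selection, linear or logistic according to scale. It names no start date, calendar period or time since onset. The only item it expressly leaves to the SAP is the definition of the analysis populations.

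**The concern.** A patient whose symptoms began two years before the assessment cannot show a five-year delay to diagnosis. Recent starters can therefore contribute only short intervals, while patients with a long history can contribute short or long ones. A setting with more recent starters shows a shorter mean even if care is identical everywhere. The same holds for endpoints 2-4, with the clock starting at diagnosis or at first csDMARD.

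The simple regression on specialty is exposed by construction. Variable selection in the multiple model cannot help, because start time is not a named candidate. What is at stake is the study's main estimate. A larger sample would only make a mixed estimate more precise.

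**Working it through.** **1. The plan's own figures reproduce (section 8.3).** With a two-sided 5% t-test:

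- 400 against 400 at effect size 0.229: 0.229/√(1/400 + 1/400) = 3.24, power 89.9%.
- 400 against 200 at 0.281: 0.281/√(1/400 + 1/200) = 3.24, power 90.0%.

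These figures are not in dispute. They set the scale: a spurious difference near 0.23-0.28 SD would be as large as the effect the study is sized to find.

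**2. Assumed inputs.** The documents give neither delay nor onset distributions, so these are assumptions. The true delay D is exponential with the same mean m in both settings (2 or 5 years). Time since onset T is uniform over 0-20 years in one setting (n = 400) and over 0-18, 0-15 or 0-10 years in the other (n = 200). There is no specialty effect.

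**3. Expected recorded mean.** Let L be the upper limit of T and k = exp(−L/m).

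- (a) Only intervals finished by the assessment are kept (D ≤ T): mean = m[L − 2m + k(L + 2m)] / [L − m(1 − k)].
- (b) Patients first diagnosed at the study assessment are kept, with a delay equal to T: mean = m[1 − (m/L)(1 − k)].

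Example for (a), m = 5:

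- L = 20, k = 0.0183: 5(10 + 0.5495)/15.092 = 3.495 years.
- L = 10, k = 0.1353: 5(0 + 2.7067)/5.677 = 2.384 years.
- Difference 1.11 years. The SDs are 3.180 and 1.979, pooled 2.836, so the spurious effect is 1.111/2.836 = 0.39 SD.

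| Onset ranges (years) | Mean delay | (a) difference, years | (a) SD units | (b) SD units |
|---|---|---|---|---|
| 0-20 vs 0-18 | 2 | 0.03 | 0.02 | 0.01 |
| 0-20 vs 0-18 | 5 | 0.16 | 0.05 | 0.04 |
| 0-20 vs 0-15 | 2 | 0.08 | 0.05 | 0.04 |
| 0-20 vs 0-15 | 5 | 0.45 | 0.15 | 0.11 |
| 0-20 vs 0-10 | 2 | 0.26 | 0.16 | 0.12 |
| 0-20 vs 0-10 | 5 | 1.11 | 0.39 | 0.30 |

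Lognormal delays (log-SD 1) under (a) give 0.02-0.05, 0.06-0.13 and 0.16-0.33 SD for the three pairs of ranges.

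**4. Test size with and without start time.** Simulation of case (a), 1,000 runs per row. The adjusted model adds T and log T, with robust standard errors.

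| Onset ranges | Mean delay | Unadjusted rejection | Adjusted rejection |
|---|---|---|---|
| 0-20 vs 0-18 | 2 / 5 | 6% / 9% | 6% / 5% |
| 0-20 vs 0-15 | 2 / 5 | 9% / 42% | 4% / 6% |
| 0-20 vs 0-10 | 2 / 5 | 45% / over 99% | 6% / 5% |

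A second illustration used gamma onset times, 400 against 400 patients and T as a linear term only. It showed the same pattern, with adjusted rejection of 4-8%.

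**5. What adjustment does not do.** The same model with a true difference in mean delay (first setting minus second):

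| True means (years) | Onset ranges | True difference | Unadjusted | Adjusted |
|---|---|---|---|---|
| 7 vs 5 | 0-20 vs 0-10 | +2.0 | +1.77 | +0.25 |
| 7 vs 5 | 0-20 vs 0-20 | +2.0 | +0.66 | +0.58 |
| 5 vs 7 | 0-20 vs 0-10 | −2.0 | +0.86 | −0.21 |

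In the first row the unadjusted figure is near the truth only because the onset gap happens to push the same way. In the third row it has the wrong sign, and adjustment restores the right one. In every row the adjusted difference is far too small, because long and unfinished intervals are still missing.

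**The case against.** **Covariates are usually left to the SAP.** That is true of details. Here, however, the protocol names its explanatory variables and describes the models built on them, and it expressly defers only the analysis populations. The parenthesis is attached to descriptive subgroups, and the list is not said to be exhaustive. Still, the next sentences refer back to those explanatory variables as the ones to be modelled.

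**Nothing in the protocol shows that onset timing differs between settings.** This stands, and it is why the size is conditional. A reader might take the expected non-confirmation rates of 10%, 15% and 25% (section 8.3) as evidence. Those rates concern patients who are excluded from the analysis and say nothing about onset among the confirmed. A reader might also point to section 3, where recommendations "have been published in the past few years in both rheumatology and dermatology". That reports publication, and the same section says it is unknown how far practice follows them. The mention of mild disease in section 4 is not a statement about recent onset.

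**Not every interval need have ended before the recruiting visit.** This also stands. Suspected patients are eligible and may be confirmed at the consulting assessment, usually within 12 weeks. If that counts as their diagnosis date, which the protocol does not say, they contribute delays close to their full time since onset. Case (b) covers this: the bias shrinks (0.39 to 0.30 SD and 0.16 to 0.12 SD) but remains.

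**The study is exploratory.** Section 8.3 says so and waives multiplicity adjustment. That lowers the weight of any single p-value, but it does not remove bias from the estimated association.

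**Conclusion.** The point holds as a conditional weakness in the stated model. If settings differ in time since the interval began, the specialty contrast in section 8.2 mixes that difference with any effect of specialty. Under the assumptions above, the spurious difference is negligible for a small gap (at most about 0.05 SD), modest for 0-20 against 0-15 years (0.04-0.15 SD), and 0.12-0.39 SD for a twofold gap. Only the twofold gap combined with the longer mean delay exceeds the planned 0.281. The documents do not say which case applies, so it cannot be concluded that the study's result will be biased by that much.

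A reader might also infer that adding start time solves the truncation problem. It does not. It removes confounding by start time and brings the test back to about its nominal size when there is no specialty effect. True differences remain strongly attenuated: about 0.25 years against a true 2.0 with unequal onset ranges, and about 0.58 even with identical ranges.

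**What to change.** In section 8.2:

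1. Include the start time of each interval, in flexible form, in every primary multiple regression model and exempt it from variable selection. Use year of symptom onset for endpoint 1, year of PsA diagnosis for endpoints 2 and 3, and year of first csDMARD for endpoint 4.
2. Report the specialty contrast from simple regression explicitly as unadjusted.
3. State that the adjustment removes confounding by start time but does not correct truncation. Unfinished intervals remain missing and true differences remain attenuated, so the adjusted estimate must not be described as corrected for truncation.

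The cost is a few sentences and a few degrees of freedom. The start dates already underlie the endpoints, so no new data are needed, and the sample size does not change.

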### 8.3. Sample Size Calculation

The factor that is most likely to influence the PsA management components of interest is clinical specialty. However, there is no scientific basis currently to judge the effect size.

So this will be an exploratory study and objectives are exploratory in nature (non-confirmatory) and no adjustment for multiplicity will be made.

With 400 evaluable patients in rheum and dermatology sites, the study has 90% power to detect a difference in means between the two specialties with a two-sample t-test at a significance level of 5% assuming an effect size of 0.229. With 400 evaluable patients in rheum or dermatology sites and 200 evaluable patients in non-rheum/non-dermatology sites, the study has 90% power to detect a difference in means between rheum vs. non-rheum/non-dermatology or dermatology vs. non-rheum/non-dermatology, respectively, with a two-sample t-test at a significance level of 5% assuming an effect size of 0.281.

The estimated drop-out rates due to non-confirmed PsA diagnosis are 10% in rheum, 15% in dermatology and 25% in non-rheum/non-dermatology sites. Hence, a total number of approximately 1200 patients (450:480:270 in rheum:dermatology:non-dermatology/non-rheum, respectively) has to be recruited in order to achieve 1000 evaluable patients (400:400:200 in rheum:dermatology:non-dermatology/non-rheum, respectively).

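### Section 8.2 selects delay intervals and estimates their effects on the same data, so for weak to moderate associations the retained slopes run too large and their ordinary 95% CIs under-cover

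*Protocol*

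**What the plan says.** Protocol section 8.2 describes two modelling steps for the research outcomes: simple regressions, one explanatory variable at a time, and then "multiple regression models with variable selection to identify and assess important explanatory variables". Results are to be reported as follows: "Effects will be estimated depending on the scale of the endpoint by use of mean differences or ORs with respective 95% confidence interval". The explanatory variables named in that paragraph are "disease severity perception by patients and physicians and clinical specialty".

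The next paragraph turns to clinical manifestation and disease burden and carries the procedure over: "Regression analyses will be done as described above, using time from symptom onset to PsA diagnosis", followed by "time from PsA diagnosis to first csDMARD, first bDMARD and from first csDMARD to first bDMAD as explanatory variables". The delay intervals therefore come under variable selection by cross-reference.

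Section 8.3 declares that "objectives are exploratory in nature (non-confirmatory) and no adjustment for multiplicity will be made".

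**The concern.** One procedure on one data set both picks the intervals and supplies their effect estimates and CIs. An interval stays in the model when its estimate in this sample is large relative to its standard error, so the estimates that survive are a favourable subset. If a correlated interval with a real effect is dropped, the remaining slope also absorbs part of that effect. An ordinary CI allows for neither.

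The first secondary objective in section 5 concerns the association between the timing of management steps and current activity and burden. The adjusted estimates for it come from these models. Each outcome may end with its own set of intervals, so an adjusted slope for HAQ-DI and one for DLQI could be adjusted for different things and not be comparable. With so few candidates and hundreds of patients, selection gains little in return.

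**Working it through.** **The plan's own figures.** The protocol gives no figure for the selection step. Its sample-size figures reproduce. With power = Φ(d·√(n₁n₂/(n₁+n₂)) − 1.96):
- d = 0.229, 400 vs 400: 0.229 × √200 = 3.239; 3.239 − 1.96 = 1.279; power 89.9%.
- d = 0.281, 400 vs 200: 0.281 × √133.3 = 3.245; 3.245 − 1.96 = 1.285; power 90.1%.

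These concern specialty comparisons and are not affected here. They supply the upper bound of 1000 evaluable patients.

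**How many intervals can enter.** Section 8.2 names four. In patients with all dates, diagnosis-to-bDMARD = diagnosis-to-csDMARD + csDMARD-to-bDMARD. A model with an intercept and all four intervals has 5 columns but rank 4 and cannot be fitted. At most three are non-redundant.

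**Assumptions, none given in the protocol.** Three standardised intervals; residual SD 1; backward elimination at p<0.05; common correlation ρ; slopes in SD of outcome per SD of interval. Bands of n: 1000 as upper bound, 300 as an illustrative subset, and 160 to 370 if bDMARD intervals exist for 16% to 37% of 1000 patients. That range is borrowed from the clinic comparison cited in section 3 and is not a forecast for this study. Each scenario used 3000 to 4000 simulated data sets.

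**Results given retention, three equal true slopes.**

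| True slope | ρ | n | Mean retained slope ÷ truth | CI coverage |
|---|---|---|---|---|
| 0.05 | 0 | 1000 | 0.083/0.05 = 1.7 | 92–93% |
| 0.05 | 0 | 300 | 0.139/0.05 = 2.8 | 78–80% |
| 0.05 | 0.3 | 1000 | 0.093/0.05 = 1.9 | about 83% |
| 0.05 | 0.3 | 300 | 0.148/0.05 = 3.0 | about 72% |
| 0.10 | 0.3 | 1000 | 0.11/0.10 = 1.1 | about 95% |
| 0.10 | 0.5 | 1000 | 1.26 | 91% |
| 0.10 | 0.5 | 370 | 1.81 | 75% |
| 0.10 | 0.5 | 160 | 2.5 | 61% |
| 0.30 | 0.5 | 370 and 1000 | 1.00–1.01 | 95% |

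The pre-set three-interval model, with every coefficient reported, covered 94.2% to 95.9% in the main set of scenarios.

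**Why dropping a correlated interval matters.** With slopes of 0.05 and ρ = 0.3, an interval left alone in the model no longer estimates 0.05. It estimates 0.05 + 2 × 0.3 × 0.05 = 0.08.

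**How much is due to selection itself.** A fair comparison reads the full model only where p<0.05, so that both sides are conditional on a significant result.

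| Scenario | Full model, read at p<0.05 | Backward elimination |
|---|---|---|
| 0.05 each, ρ=0, n=300 | 0.139, 79.6% | 0.139, 80.0% |
| 0.05 each, ρ=0, n=1000 | 0.083, 92.6% | 0.083, 92.7% |
| 0.05 each, ρ=0.3, n=1000 | 0.089, 92.1% | 0.093, 84.0% |
| one interval at 0.05, others 0, ρ=0.3, n=1000 | 0.089, 91.5% | 0.085, 92.2% |

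In the third row the average inflation is nearly the same on both sides. The full model read selectively loses about 95 − 92.1 = 2.9 points of coverage, and elimination loses a further 92.1 − 84.0 = 8.1. That extra loss did not appear when the intervals were uncorrelated or when only one had an effect.

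**The case against.** Several counter-arguments carry weight.

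- **Unselected estimates are also planned.** The simple models give each interval a slope and CI for every outcome. This stands, so the secondary objective does not rest on selected models alone. Those slopes are not mutually adjusted, so they cannot replace a pre-set multiple model.
- **Much of the inflation is the winner's curse.** This stands: it also arises when a full model is read only at p<0.05. It does not defend reporting retained terms only, because a selected model shows nothing else.
- **False findings under the null.** A reader might infer that selection creates spurious intervals, since with no true association about 14% of outcomes retain at least one. The full model shows about the same, as 1 − 0.95³ = 14.3%. That is multiplicity, which section 8.3 openly leaves unadjusted. That a retained null interval's CI excludes zero follows from a p<0.05 rule by construction.
- **Exploratory status.** Section 8.3 states it plainly and it limits the consequence. It does not repair a biased slope or an under-covering CI, which are the main product of an exploratory study.
- **The rule may be in the SAP.** The SAP is not shown, so the missing criterion is no finding. That selection precedes estimation is already fixed in section 8.2. A looser rule (p<0.157) lessens the problem without removing it: at slope 0.05, ρ=0.3 and n=300, slopes are still 2.3 times the truth with 84% coverage.

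**Conclusion.** The point holds for weak to moderate associations. For a true slope of 0.05 SD at correlation 0.3, CIs of retained intervals cover about 83% at n=1000 and 72% at n=300, with slopes about 1.9 and 3 times too large. These sizes rest on the assumed elimination rule, slopes and correlations.

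A reader might go further and infer that every retained estimate is wrong. The calculations do not support that. Slopes of 0.30 SD are unaffected at ρ = 0.5. Slopes of 0.10 SD at n=1000 are barely affected at ρ = 0.3 and moderately at ρ = 0.5. Coverage given retention can exceed 95%. With negatively correlated intervals (ρ = −0.3) some strong slopes shrink instead (ratio 0.93, coverage 87% to 89%). In absolute terms the weak effects stay weak: with the other intervals held fixed, 0.05 SD explains about 0.05² = 0.25% of variance, and 0.093 SD about 0.9%.

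The change is still worth making. Three non-redundant candidates need no data-driven selection, and the remedy costs almost nothing.

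**What to change.** In section 8.2, remove variable selection from the secondary regressions on delay intervals and pre-specify the models:

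- Use at most three non-redundant intervals, and name in advance which of the three linked treatment intervals is left out.
- State the patient set for each model, because treatment intervals exist only in treated patients. For example: (a) symptom-to-diagnosis delay in all patients with confirmed PsA; (b) that delay plus diagnosis-to-csDMARD in csDMARD-treated patients; (c) both plus csDMARD-to-bDMARD in patients with both dates. A single three-interval model for everything would confine every analysis to the last group.
- Use the same models and adjustment variables for every outcome, and report every coefficient with its 95% CI whatever its p-value.
- Show any selected model only as hypothesis-generating.

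This takes a few sentences in the protocol or SAP and no extra data or patients. CIs become slightly wider, and models with bDMARD intervals rest on the smaller treated subset. Full reporting also does not remove multiplicity: readers who look only at significant coefficients will still meet the winner's curse.
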